### Randomization and blinding

An independent biostatistician, not involved in data management or analysis, generates the randomization list using a validated online tool^1^. The randomization is carried out using a 1:1 allocation ratio and permuted blocks of sizes 2 and 4. The allocation sequence will be executed using a password-protected, web-based randomization module. The encrypted database can be accessed only by an unblinded trial nurse. Based on the randomization list, the nurse will prepare and distribute the study medications (rocuronium or normal saline placebo) in identically labeled syringes marked only with study numbers. It is visually impossible to distinguish the contents of these syringes because both rocuronium and normal saline are clear and colorless solutions. Patients, endoscopists, outcome observers, researchers responsible for recording the data, and data analysts will all be kept blinded to the group assignment until the final analysis is finished. Due to safety considerations and the necessity of monitoring the train-of-four (TOF) ratio, the primary anesthetist, responsible for administering anesthesia to the patients as well as monitoring the TOF ratio at the ulnar nerve, is unblinded to the group assignments. However, the primary anesthetist neither knows the hypothesis of this study nor participates in outcome assessment. The patient recruitment, study interventions, and outcome measurement schedule are presented in Table 1.

**TABLE 1 T1:** Schedule of patient enrollment, study intervention, and endpoint measurement.

Timepoint	Study period				
	Enrollment	Allocation	Post-allocation		
	Preanesthetic visit	Before operation	During operation	PACU	24 h after the operation
Enrollment	×	×			
Inclusion criteria	×				
Exclusion criteria	×				
Written informed consent	×				
Baseline characteristics	×				
Preoperative cough status	×				
Randomization					
Allocation		×			
Intervention					
Group rocuronium			×		
Group normal saline			×		
Endpoint measures					
Frequency of coughing episodes			×	×	×
Cumulative remifentanil dosage			×		
Failure rate			×		
Hemodynamic variables			×		
Cough scores in the PACU			×		
Procedure time				×	
Discharge time			×		
Adverse events				×	
Satisfaction scores of bronchoscopist			×	×	
Satisfaction scores of anesthesiologist					
Satisfaction scores of parents					

According to SPIRIT 2013 statement of defining standard protocol items for clinical trials. PACU, post-anesthesia care unit.

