## Methods

### Study design

This single-center, double-blind, randomized, placebo-controlled trial will be conducted at Children’s Hospital of Soochow University, Suzhou, China. This trial protocol follows the guidelines of Standard Protocol Items: Recommendations for Interventional Trials (SPIRIT) (Supplementary File 1).

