### Study interventions

#### Anesthesia preparation stage

All children are screened for eligibility by an experienced anesthesia assistant who will not be involved in block sizes and future allocation. Baseline data including heart rate (HR), systolic blood pressure (SBP), diastolic blood pressure (DBP), pulse oxygen saturation (SpO_2_) are recorded. Children with a diagnosis of pneumonia or airway foreign body but with a stable, improving, or predictable pattern of cough will be eligible for inclusion. Their baseline cough frequency (“occasional” or “frequent but stable”) will be recorded as a characteristic for group comparison. Children are restricted from consuming solid foods for 6 h and clear fluids for 2 h prior to undergoing FFB (26). A patent intravenous cannula is inserted, and premedication with intravenous midazolam at a dose of 0.05 mg⋅kg^–1^ is given in the ward. Topical anesthesia is achieved by administering a 2-milliliter nebulized 2% lidocaine solution through inhalation before the procedure in the ward.

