#### Anesthesia induction stage

All FFB procedures are carried out in the outpatient bronchoscopy room with children positioned in a supine position. Throughout the procedures, HR, end-tidal partial pressure of carbon dioxide (PetCO_2_), SpO_2_, body temperature and the bispectral index (BIS) are continuously monitored and noninvasive blood pressure (NIBP) is measured at 3-min intervals. Anesthesia depth is monitored using a combination of standard clinical signs and BIS. The BIS is a dimensionless number ranging from 0 to 100, which is calculated based on frontal electroencephalographic signals. The primary goal is maintaining clinical signs of adequate anesthesia, defined by the absence of purposeful movement or gross sympathetic response (tachycardia > 20% above baseline or hypertension > 20% above baseline). The BIS value of 40–60 serves as a secondary guide, which is intended as an adjunctive, quantitative tool to minimize the risk of awareness and help maintain a relatively stable hypnotic state. A nasopharyngeal temperature probe is promptly placed after the induction of anesthesia, and temperature readings are documented at 3-min intervals throughout the entire case. Normothermia is precisely defined as a core temperature ranging from 36.0 °C to 37.5 °C. To effectively maintain normothermia, a forced-air warming blanket that is set at a temperature between 32 °C and 43 °C is available if needed. In the event that body temperature falls below 36.0 °C, the forced-air warmer temperature is increased. No patient is discharged from the operating room with a body temperature < 35.5 °C. TOF ratio is monitored immediately prior to the insertion of LMA and upon the completion of the procedure. All participants receive anesthesia that is administered by the same primary anesthesiologist. Following the intravenous administration of propofol at a dosage of 3 mg⋅kg^–1^, TOF stimulation is delivered at 15-s intervals. After 2 min of stable readings, the baseline twitch height is set to 100% for calibration. Then, remifentanil is administered at a dosage of 3 μg⋅kg^–1^. As spontaneous breathing gradually subsides, manual mask ventilation with 100% oxygen is provided as a supportive measure. Subsequently, an intravenous dosage of rocuronium at 0.3 mg⋅kg^–1^ is administered to the rocuronium group, while an equivalent volume of normal saline is given to the normal saline group. Immediately after the administration of all the induction drugs, remifentanil is infused at an initial rate of 0.05 μg⋅kg^–1^⋅min^–1^ (7). After 60 s of the administration of rocuronium or normal saline, the TOF ratio is recorded, and an appropriately sized LMA is inserted. The LMA is then connected to an anesthesia machine to manage ventilation in synchronized intermittent mandatory ventilation mode with a tidal volume of 6 ml/kg and adjust the breathing rate to maintain PetCO_2_ at 30–40 mmHg. Oxygen is delivered at a concentration of 50% and a flow rate of 2 L/min. Meanwhile, sevoflurane is titrated with an initial concentration of 1.5% through the LMA to maintain the appropriate anesthesia depth. If the clinical signs are adequate but the BIS values persistently exceed 60, the concentration of sevoflurane is increased in 0.5% increments. Conversely, if the BIS values are within or below the target range but the clinical signs suggest light anesthesia (such as movement, tachycardia or hypertension), the clinical signs take precedence, and the concentration of sevoflurane is increased in 0.5% increments. No reduction in the sevoflurane concentration is made solely based on a low BIS value if the clinical assessment indicates an adequate depth of anesthesia.

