#### Sample size

In a previous study by Tschiedel et al. comparing the use of propofol alone versus propofol combined with remifentanil during FFB, the addition of remifentanil resulted in a reduction of coughing episodes by approximately 60%, from 1.98 to 0.73 episodes per minute (1). Before implementing this trial, we prospectively studied 20 children undergoing FFB from April 2025 to May 2025. Our findings revealed that the frequency of cough episodes in children using the propofol-remifentanil regimen ranged from 0.6 to 0.89 episodes per minute, with a standard deviation (SD) of 0.3 episodes per minute, which is consistent with previously published data. Another 50% reduction in coughing episodes, decreasing the frequency to 0.3 episodes per minute with rocuronium, represents not only a statistically significant difference but also a clinically relevant improvement. We will require 64 subjects per group to achieve a power of 0.80 with a type I error rate of 0.05. Accounting for an anticipated dropout rate of 10%, the adjusted estimated sample size will be 70 children per group, resulting in a total of 140 children being randomized.

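### Blocks of 2 and 4 on one single-center list make allocation more guessable than it need be for the unblinded anesthetist; larger, withheld block sizes are a cheap improvement

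*Protocol article*

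**What the plan says.** The section on randomization and blinding fixes a 1:1 ratio in "permuted blocks of sizes 2 and 4". It names no stratification factor, so there appears to be one list. The study design section describes a single-center trial, and the sample size section plans for "resulting in a total of 140 children being randomized".

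Two people know past allocations. For the trial nurse who prepares the syringes, the text reads "The encrypted database can be accessed only by an unblinded trial nurse". The primary anesthetist "is unblinded to the group assignments", and the induction section adds: "All participants receive anesthesia that is administered by the same primary anesthesiologist". One clinician in the procedure room therefore sees the whole sequence as it unfolds.

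Safeguards are stated too. The children are screened by an anesthesia assistant "who will not be involved in block sizes and future allocation". Consent is presented by the principal and associate investigators. The anesthetist is said not to know the hypothesis and not to assess outcomes. The article does not say whether the two block sizes are mixed at random, in what proportion, or whether the anesthetist is kept unaware of them.

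**The concern.** Two is the smallest block size possible in a 1:1 trial. If a block is known to be of size 2, its second allocation follows from its first. A block of 4 gives away its last allocation, and sometimes its last two. The sizes are in print, and one person sees every allocation on one list. That person can predict upcoming allocations well above chance.

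What would be at stake is allocation concealment. If someone who decides on eligibility, approaches parents or orders the day's cases learns which arm is likely next, the choice of children can depend on the arm. Some eligibility criteria leave room for judgement: a parent's estimate of a doubling in cough, and tonsils or adenoids that might affect mask placement.

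**Working it through.** The article states no predictability figure, so there is none to reproduce.

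**Inputs from the article:** 1:1 ratio, blocks of 2 and 4, one center, no stratification stated, 140 children, and one anesthetist who knows all past arms.

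**Assumptions:** block sizes are drawn at random per block, in equal proportion as the base case and with 25% to 75% of size 2 as the range. The guesser knows the set of sizes but not their order.

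**1. Overall guess rate (exact).** The best guess is the arm that is behind, with a coin toss when the arms are level. In a block of size 2b, the expected number of level positions is T = 4^b / C(2b,b) − 1, and the expected number of correct guesses is b + T/2.

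| Block size | T | Expected correct |
|---|---|---|
| 2 | 4/2 − 1 = 1 | 1.5 |
| 4 | 16/6 − 1 = 1.667 | 2.833 |
| 6 | 64/20 − 1 = 2.2 | 4.1 |
| 8 | 256/70 − 1 = 2.657 | 5.329 |

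- Blocks 2 and 4, equal mix: (1.5 + 2.833)/6 = 72.2%.
- 25% of size 2: (0.25 × 1.5 + 0.75 × 2.833)/(0.25 × 2 + 0.75 × 4) = 2.5/3.5 = 71.4%.
- 75% of size 2: (0.75 × 1.5 + 0.25 × 2.833)/(0.75 × 2 + 0.25 × 4) = 1.833/2.5 = 73.3%.
- Blocks 4, 6 and 8, equal mix: (2.833 + 4.1 + 5.329)/18 = 68.1%.
- Simple randomization: 50%.

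**2. Coin tosses.** With an equal mix of 2 and 4, (1 + 1.667)/6 = 44.4% of allocations fall when the arms are level and cannot be predicted. In the remaining 3.333 of every 6, the guess is right 3 times, or 90%.

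**3. Confidence of individual calls.** This was obtained by simulating 140-child lists, with the guesser updating by Bayes' rule after each child.

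| Design | Correct | Confidence ≥ 0.80 | Confidence ≥ 0.90 | Certain |
|---|---|---|---|---|
| 2/4, 25% of size 2 | 71% | 44% | 20% | 14% |
| 2/4, equal mix | 72% | 55% | 16% | 11% |
| 2/4, 75% of size 2 | 73% | 53% | 53% | 7% |
| 4/6/8, equal mix | 68% | 24% | 5% | 2% |

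The simulated guess rates agree with step 1.

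**4. Why the 80% share depends on the mix.** At the start of a list, once the first child's arm is known, confidence in the second is p × 1 + (1 − p) × 2/3, where p is the share of size-2 blocks. This is 0.83 at p = 0.5, 0.75 at p = 0.25 and 0.92 at p = 0.75. A cut at 0.80 lies just below the base-case value.

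**The case against.** The strongest case on the other side has four parts.

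**The person who can predict has no stated use for the prediction.** The anesthetist already knows the current child's arm, so guessing it adds nothing to how that child is treated. Foreknowledge matters only through enrollment or scheduling. The article gives screening and consent to others, keeps the list in a restricted module, and says the anesthetist does not know the hypothesis. This stands. That the anesthetist can influence who proceeds, or when, is something a reader might infer from a small team, but no section says so.

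**The size depends on the threshold and the mix.** A reader might conclude that most allocations can be predicted with high confidence. At 0.80 that is a bare majority in the base case and falls to 44% if a quarter of blocks are of size 2. At 0.90 it is 16% in the base case. The comparison with larger blocks also depends on the cut: at 0.70, blocks of 4, 6 and 8 are callable slightly more often (about 61% against 55%). The one measure without a cut, the overall guess rate, differs by about 4 points. This stands too.

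**Observer blinding is a different matter.** A reader might carry the figures over to the blinded observer or bronchoscopist, on whom the primary endpoint rests. The figures assume that every past arm is known with certainty, which does not hold for blinded staff. If coughing or sugammadex use reveals an arm, it reveals the current child's arm whatever the block size.

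**An article may omit detail.** Random variation of the block sizes and who is told of them may be set out in the full protocol. Silence on these is therefore not counted as an error. The sizes themselves, however, are a stated rule.

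**Conclusion.** The point holds as a cheap improvement, not as a demonstrated flaw in concealment. With blocks of 2 and 4 on one list, a person who sees every past allocation could guess about 72% of them (71–73%), call about 55% with at least 80% confidence (44–55%) and be certain of 11% (7–14%), while about 45% remain coin tosses. Blocks of 4, 6 and 8 bring this to 68%, 24% and 2%. The benefit is modest overall and consists mainly of fewer near-certain calls.

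These figures rest on a single unstratified list, a random mix of sizes and full knowledge of past arms. They become a risk to concealment only if foreknowledge passes from the anesthetist to those who screen, consent or schedule. The documents do not support the stronger readings that allocation has been compromised, or that the small blocks unblind the observer or bronchoscopist.

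**What to change.** For the list, or for its unused remainder if recruitment has begun:

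1. Drop block size 2 and use randomly varying blocks of 4, 6 and 8.
2. Withhold the new sizes from all site staff, including the primary anesthetist, until database lock. The present sizes are already published, so withholding works only together with a change. It hides which calls are near-certain, but it does not stop someone from guessing the arm that is behind.
3. State that the unblinded anesthetist has no part in screening, consent or scheduling, and does not pass on past allocations to those who do.

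The cost is regenerating the list and a possible end-of-trial difference of up to 4 children between arms instead of 2 (half the largest block, if enrollment ends within it). That is negligible with 70 per arm. Sample size, endpoints and clinical procedures do not change.

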
#### During the procedure

An Olympus BF-XP290 flexible fiberoptic bronchoscope with an outer diameter of 2.8 mm, or a BF-P290 with an outer diameter of 4.0 mm is inserted through the bronchoscope connector. The suction port is sealed with a Polyvinyl Chloride cover to create an airtight seal around the bronchoscope. When the vocal cords are visualized, 2% lidocaine, usually administered in a volume of 1 mL, is applied to the vocal cords via the bronchoscope to prevent laryngospasm. Then, the vocal cords are carefully traversed, and 1 ml of 2% lidocaine is instilled into the tracheobronchial tree using the “spray as you go” technique (27). Further diagnosis and treatment of the airway using a flexible bronchoscope is performed based on the specific clinical context. The infusion rate of remifentanil is adjusted every minute, increasing or decreasing by 0.01 μg⋅kg^–1^⋅min^–1^ based on any signs of coughing. If a cough reaction occurs, the infusion rate is increased; if no cough reaction is observed, the infusion rate is decreased, as determined by the primary anesthesiologist. Supplemental boluses of 1–2 μg⋅kg^–1^ remifentanil will be administered as a remedy and repeated as needed in the event of persistent coughing. If blood pressure or other hemodynamic parameters preclude the administration of adequate doses of remifentanil, a supplementary dose of rocuronium (0.2 mg⋅kg^–1^) is administered. Cases in which a supplementary dose of rocuronium is administered are defined as those “with the highest incidence of coughing” and are categorized as “failure cases.”

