### Secondary endpoints

The secondary endpoints are: (1) cumulative remifentanil dosage; (2) success rate of FFB operation; (3) hemodynamic variables; (4) cough scores in the PACU every 5 min; (5) procedure time defined as the duration from bronchoscope insertion to its removal; (6) discharge time which is defined as the interval from the removal of bronchoscopy until a modified Aldrete score of ≥9 is achieved; (7) adverse events that occur during the procedure and in the PACU, including desaturation (SpO_2_ < 90%) which is stratified into three categories: mild desaturation: 85% ≤ SpO2 < 90%, moderate desaturation: 80% ≤ SpO2 < 85%, severe desaturation: SpO2 < 80%; laryngospasma; sore throat; bradycardia or hypotension defined as a decrease of at least 20% below the age-adjusted lower limit of heart rate or arterial blood pressure; tachycardia or hypertension defined as an increase of at least 20% above the age-adjusted upper limit of heart rate or arterial blood pressure; (8) satisfaction scores of bronchoscopists during the operation; (9) satisfaction scores of anesthesiologists; (10) satisfaction scores of parents 24 h after the operation. Given the age range of our study population (1–6 years), this score is reported as a proxy measure by the child’s parent or guardian, who is present throughout the preoperative, recovery, and immediate post-discharge periods. Satisfaction scores are measured subjectively by a simple numeric score between 1 (highly dissatisfied) and 10 (highly satisfied).

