### Data collection and management

Demographic data include sex, age, weight, height, and BMI. Baseline characteristics encompass ASA physical status, as well as baseline values for HR, NIBP, SpO_2_, and baseline cough frequency (“occasional” or “frequent but stable”). Periprocedural data include the following: the total number of coughing episodes during the FFB intervention period; procedure time; cumulative remifentanil dosage; success rate of the FFB operation; HR, NIBP, SpO_2_, PetCO_2_, body temperature, BIS value, severity grading of pneumonia; the usage and dosage of sugammadex, the corresponding TOF ratio at the time of reversal; cough scores recorded in the PACU; discharge time; and adverse events that occurs during the procedure and in the PACU, including desaturation (SpO_2_ < 90%), laryngospasm, sore throat, bradycardia or hypotension, tachycardia or hypertension. Additionally, the data will capture anesthesiologist satisfaction, bronchoscopist satisfaction and parent satisfaction. All raw data will be meticulously documented in the Case Report Forms (CRFs) by an independent investigator. Upon completion of the trial for all patients, the principal investigator and the data administrator will jointly verify the integrity and accuracy of the data. Subsequently, the data administrator will import the verified data into a designated electronic database and forward it to a statistician for final statistical analysis.

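### The unblinded anesthetist is said to assess no outcome but on the natural reading rates secondary endpoint 9, and reversal data can unmask recorders and analysts for some children

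*Protocol article*

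**What the plan says.** All places are in the protocol article.

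- **Randomization and blinding.** The primary anesthetist "is unblinded to the group assignments", for reasons of safety and TOF monitoring. The section adds, without qualification, that "the primary anesthetist neither knows the hypothesis of this study nor participates in outcome assessment". It also promises: "Patients, endoscopists, outcome observers, researchers responsible for recording the data, and data analysts will all be kept blinded to the group assignment", and this is to last until the final analysis is complete.
- **Anesthesia induction stage.** "All participants receive anesthesia that is administered by the same primary anesthesiologist".
- **Secondary endpoints.** Item 9 is "satisfaction scores of anesthesiologists", a subjective numeric score from 1 to 10. The rater is not identified.
- **During the procedure.** The remifentanil rate goes up with cough; without cough "the infusion rate is decreased, as determined by the primary anesthesiologist". Boluses are given for persistent coughing, which is not defined. Supplementary rocuronium depends on a hemodynamic judgement with no stated threshold, and giving it makes the case a failure.
- **Anesthesia recovery stage.** The primary anesthesiologist decides on reversal.
- **Data collection and management.** The periprocedural data include "the usage and dosage of sugammadex, the corresponding TOF ratio at the time of reversal". An independent investigator writes all raw data in the case report forms, and the verified database goes to the statistician. No separate handling of the reversal items is described.

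**The concern.** The article describes the trial as double-blind and supports this with two specific assurances: the one unblinded clinician assesses no outcome, and those who record and analyze the data do not know the arm. Other sections do not bear out either assurance in full.

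A subjective satisfaction score from someone who knows whether rocuronium was given is open to expectation. If it is reported beside the bronchoscopist's blinded score with no distinction, readers will give the two equal weight. Two further secondary endpoints, remifentanil dose and failure, depend partly on decisions by the same clinician.

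Analyst blinding matters here because the Statistical analysis section lets the observed distribution of the primary endpoint decide the model: negative binomial regression in one case, multiple linear regression in the other. An analyst who can tell which coded group is rocuronium would make that choice with the allocation in view.

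**Working it through.** The article gives no figure to reproduce. The first two checks set sections side by side; the third is an illustration with assumed rates.

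**1. Endpoint 9 against the blinding sentence**

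- The primary anesthetist is unblinded (Randomization and blinding).
- One primary anesthesiologist anesthetizes all participants, 140 planned (Anesthesia induction stage; Sample size).
- Endpoint 9 is an anesthesiologist's own subjective score (Secondary endpoints).
- No other anesthesiologist is described as present.

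Together, 140 of 140 planned values of endpoint 9 come from a single unblinded rater. Supplying a subjective endpoint score is outcome assessment, so the unqualified sentence does not hold for this endpoint.

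**2. Cumulative remifentanil and failure**

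The text assigns rate changes to the primary anesthesiologist. It names nobody for the supplementary rocuronium decision; that this is the same person follows only from the role of administering the anesthesia. Both are decisions about treatment, not ratings. They do not contradict the sentence, but they let knowledge of the arm influence what is later counted.

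**3. Reversal data**

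Inputs: 70 children per arm and 1:1 allocation (from the article); q and s, the reversal rates under rocuronium and saline (assumed, because the article gives neither). A saline child could be reversed after supplementary rocuronium, so s need not be 0.

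- P(at least one reversal among 70 rocuronium children) = 1 − (1 − q)^70
- P(rocuronium | reversed) = q / (q + s)

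| q | Expected reversed, 70q | P(at least one) | P(rocuronium given reversed), s = 0 | Same, s = 5% |
|---|---|---|---|---|
| 5% | 3.5 | 97.2% | 100% | 50% |
| 10% | 7 | 99.9% | 100% | 67% |
| 20% | 14 | >99.9% | 100% | 80% |
| 50% | 35 | >99.9% | 100% | 91% |

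For example, 1 − 0.95^70 = 0.972, and 0.20 / (0.20 + 0.05) = 0.80.

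Per child the leak is partial. Someone who guesses rocuronium for each reversed child and saline for every other is right with probability 0.5q + 0.5(1 − s). With s = 0 that is 52.5% at q = 5%, 60% at q = 20% and 75% at q = 50%, against 50% by chance. In aggregate, a clear excess of reversals in one coded group would tell the analyst which group is rocuronium. If q and s were equal, reversal would carry no information.

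**The case against.** The strongest reply has four parts.

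- **The unblinded role is disclosed and justified, and the clinician is said not to know the hypothesis.** This is true and lessens the concern. It does not make the score blinded: the rater still knows which drug each child received.
- **The rater is never named, and the endpoint is worded in the plural.** This stands as a caveat. If a second, blinded anesthesiologist gives the scores, the article should say so, because no such person is described.
- **Titration and rescue deliver treatment; they do not assess outcomes.** This is correct. A reader might infer that control over remifentanil and rescue also proves the sentence false, or that the primary endpoint is assessed unblinded. The text supports neither. A dedicated blinded observer scores cough, and the blinded bronchoscopist confirms interference with the procedure.
- **Reversal is conditional, and masking of data fields is often left to a fuller document.** Part of this stands. A reader might infer that the case report form reveals the arm of every child. It does not: the listed items concern reversed children, spontaneous recovery is expected in most, and the list does not include the TOF reading taken 60 s after the study drug. But the article itself promises blinded recorders and analysts and then describes a data flow at odds with that promise. The statistician receives the data only after all patients have finished, which does not help, since the promise runs to the end of the final analysis.

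Two further inferences should be resisted. Sevoflurane is raised partly on movement, which the block can suppress, but that would happen with a blinded anesthetist too, so it is not a blinding defect. Nor does comparing one remifentanil bolus with the infusion total at the starting rate measure the bias, because the rate changes every minute.

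**Conclusion.** The concern holds in a limited form.

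- **Endpoint 9:** the blinding sentence is inaccurate for one of ten secondary endpoints, affecting all 140 planned scores. This assumes that the rater is the primary anesthesiologist, which is the natural reading but is not stated.
- **Remifentanil dose and failure:** not fully protected by blinding. The influence is explicit for remifentanil and inferred for failure. This is a limit on interpretation, not a contradiction.
- **Recorders and analysts:** their blinding can be broken for reversed children and, through imbalance, at the level of the coded groups. How far depends on reversal rates that the article does not give; the rates used above are assumptions.
- **Primary endpoint:** its assessment stays with a separate blinded observer. The remaining exposure is the data-dependent choice of model by an analyst who may have seen reversal data.

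This should be corrected before analysis. It does not undermine the assessment of the main outcome.

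**What to change.** 1. Rewrite the sentence in Randomization and blinding so that it no longer covers endpoint 9. Name who rates anesthesiologist satisfaction and whether that person knows the arm.
2. Report anesthesiologist satisfaction as an unblinded, exploratory measure, or drop it.
3. State that cumulative remifentanil and failure are influenced by an unblinded clinician, and interpret them accordingly. The investigators should reconcile the section During the procedure with the blinding statement. No change to any dosing or rescue rule is proposed here.
4. Put TOF and sugammadex data on a separate form held by the trial nurse, who is already unblinded. Withhold it from the blinded recorders and analysts until the primary analysis is locked.

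The cost is some rewording and one extra form. The downside is that one secondary endpoint loses its blinded status.
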